## Abstract

*Objective*. Sublingual microcirculatory alterations are associated with an adverse prognosis in several critical illness subgroups. Up to now, single-center studies have reported on sublingual microcirculatory alterations in ICU patient subgroups, but an extensive evaluation of the prevalence of these alterations is lacking. We present the study design of an international multicenter observational study to investigate the prevalence of microcirculatory alterations in critically ill: the Microcirculatory Shock Occurrence in Acutely ill Patients (microSOAP). *Methods*. 36 ICU's worldwide have participated in this study aiming for inclusion of over 500 evaluable patients. To enable communication and data collection, a website, an Open Clinica 3.0 database, and image uploading software have been designed. A one-session assessment of the sublingual microcirculation using Sidestream Dark Field imaging and data collection on patient characteristics has been performed in every ICU patient >18 years, regardless of underlying disease. Statistical analysis will provide insight in the prevalence and severity of sublingual alterations, its relation to systemic hemodynamic variables, disease, therapy, and outcome. *Conclusion*. This study will be the largest microcirculation study ever performed. It is expected that this study will also establish a basis for future studies related to the microcirculation in critically ill.

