### 2.7. Data Analysis

#### 2.7.1. Sample Size Calculation

Because this is the first extensive prevalence study on microcirculatory alterations ever done, with a primarily explorative character, a concise power calculation is virtually impossible. Based on previous studies, with a sample size between 25 and 50 patients, in heart failure, high-risk noncardiac surgery, sepsis, and paediatric ICU patients, significant correlations between the existence of microcirculatory alterations and parameters of morbidity and mortality could be established [6, 10, 12]. However, it is reasonable to assume that morbidity and mortality may be lower in a general ICU population. Therefore, we aim for a sample size ten times larger than previously reported in single-center subgroup studies. Since this is by far the largest cohort of in vivo microcirculatory research in humans ever done, practical limitations with respect to availability of SDF/OPS technique and skilled operators will undoubtedly play a significant role in the definitive sample size.

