#### 2.7.2. SDF/OPS Image Analysis

The SDF/OPS image analysis will be performed by the researchers appointed by the initiators of this study in accordance with internationally accepted guidelines using dedicated software [34, 35]. The analysis will be conducted blinded to the origin of the film clips. In a suitable subgroup, an automatic assessment method will be performed as described elsewhere to investigate the suitability of such an automatic software for evaluation and quantification of microcirculatory alterations [40].

Due to the demanding imaging technique, quality of SDF images may vary between centers [41]. However, up-to-date externally validated image quality scoring systems appear to be lacking. To ensure consistency in SDF analysis, SDF analysis will be performed by researchers appointed by the principal investigators, taking care for ongoing feedback and aiming for consensus. Since several reports from different research groups have reported excellent inter- and intraobserver agreement for the SDF image analysis, the steering committee decided beforehand that this would not be an extra topic of this study [5, 10, 34].

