Secondary outcome parameters are the correlation between microcirculatory changes and macrohaemodynamic variables, correlations between microcirculatory changes, and length of ICU/hospital stay, mortality, and SOFA/APACHE II scores [45, 46]. Differences between several subgroups will be assessed using a *t*-test in case of normally distributed variables; in case of non-normally distributed variables, a nonparametric test will be chosen. Whenever applicable, forward stepwise logistic regression analysis will be used to test for associations between the severity of microcirculatory dysfunction and illness severity, mortality, and length of stay. In addition, the relation between microcirculatory alterations, applied therapy (e.g., fluid therapy and vasopressor therapy), and indicators of peripheral perfusion (e.g., lactate) will be explored. Furthermore, the geographical distribution of microcirculatory alterations will be assessed.

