## 4. Conclusion

With an anticipated inclusion rate of approximately 500 patients, this study will provide the largest reported database of clinical in vivo microscopy in critically ill patients. We expect that this study will form a solid basis for a deeper understanding of the prevalence and meaning of microcirculatory alterations in intensive care patients and show the way forward to the design of a goal-directed interventional study based on the normalization of microcirculatory alterations in intensive care patients.

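### The named analysis methods carry no centre term, so an unadjusted prevalence interval or region comparison across 36 ICUs would understate uncertainty

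*Protocol article*

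**What the plan says.** Section 2.7.3 makes the prevalence of microcirculatory alterations the primary outcome. It names no interval or variance method for it. Subgroup differences are to be tested with a t-test for normally distributed variables, and "in case of non-normally distributed variables, a nonparametric test will be chosen". Forward stepwise logistic regression, where applicable, is to relate the severity of microcirculatory dysfunction to illness severity, mortality and length of stay. The section then adds: "Furthermore, the geographical distribution of microcirculatory alterations will be assessed". No test is named for this. No centre effect, stratification by centre, random effect or cluster-robust variance appears anywhere in the article.

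The Abstract describes the structure of the sample: "36 ICU's worldwide have participated in this study aiming for inclusion of over 500 evaluable patients". The Conclusion repeats the target: "With an anticipated inclusion rate of approximately 500 patients".

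On differences between centres, section 2.7.2 states: "Due to the demanding imaging technique, quality of SDF images may vary between centers". It adds that externally validated quality scores appear to be lacking. Two safeguards are described. The Methods paragraph on ICU selection, before section 2.2, asks for demonstrated skill and/or publications and for sample videos on which feedback is given. Section 2.7.2 has the clips read by appointed researchers who do not know where they came from.

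**The concern.** Patients in the same ICU share operators, equipment, local choice of the clip segment to submit (section 2.6), case mix and treatment habits. Their microcirculatory measurements may therefore resemble each other more than those of patients from different ICUs. Methods that assume independence ignore this.

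Two stated aims are exposed:

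- **The primary prevalence.** It is pooled over ICUs, so its variance includes the between-ICU variance. A binomial standard error leaves that out.
- **The geographical comparison.** It is planned in section 2.7.3 and is also one of the study questions in the Discussion. Each ICU lies in one region, so region is a between-centre factor whose information is limited by 36 centres rather than 500 patients.

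At stake is whether the prevalence is published with more precision than the data support, and whether ordinary variation between ICUs is reported as a regional difference. The Conclusion intends the results as the basis for an interventional study.

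**Working it through.** **Inputs from the article**

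- 36 ICUs and about 500 patients (Abstract, Conclusion).
- Basis of the target: earlier studies "with a sample size between 25 and 50 patients" and the statement "we aim for a sample size ten times larger than previously reported in single-center subgroup studies" (section 2.7.1).

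**Assumptions, not in the article**

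- ICC of 0.02, 0.05 or 0.10.
- A prevalence of 20%, for illustration.
- Two-sided 5% tests and 95% intervals.

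**1. The plan's own figure.** 10 × 50 = 500 reproduces the target; 10 × 25 = 250 does not. The target is thus ten times the upper end of the earlier range, a rule of thumb with no allowance for clustering.

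**2. Design effect.** Mean cluster size m = 500/36 = 13.9, and DE = 1 + (m − 1) × ICC.

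- ICC 0.02: 1 + 12.9 × 0.02 = 1.26
- ICC 0.05: 1 + 12.9 × 0.05 = 1.64
- ICC 0.10: 1 + 12.9 × 0.10 = 2.29

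**3. Consequences.** Effective N = 500/DE. Coverage of a naive 95% interval = 2Φ(1.96/√DE) − 1. The error of a naive 5% test of a two-level centre-level factor is one minus that coverage. The half-width at 20% prevalence is 1.96 × √(0.20 × 0.80 × DE/500); without clustering it is 3.5 points.

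| Assumed ICC | DE | Effective N | Coverage of naive 95% interval | Error of naive 5% test | Correct half-width (points) |
|---|---|---|---|---|---|
| 0.02 | 1.26 | 398 | 92% | 8% | 3.9 |
| 0.05 | 1.64 | 304 | 87% | 13% | 4.5 |
| 0.10 | 2.29 | 218 | 80% | 20% | 5.3 |

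**4. Unequal ICU sizes.** With an assumed coefficient of variation of 0.6 in ICU size, DE = 1 + ((0.6² + 1) × m − 1) × ICC, which gives 1.36 / 1.89 / 2.79. The table is therefore on the mild side if ICUs recruit unevenly.

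**5. Which comparisons are affected.** A simulation (3000 runs per setting, 36 ICUs of 13 or 14 patients, normally distributed outcome, no true difference) gave these rejection rates for naive 5% tests:

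| Comparison | ICC 0.02 | ICC 0.05 | ICC 0.10 |
|---|---|---|---|
| Two regions of whole ICUs, t-test | 7.7% | 12.5% | 18.3% |
| Four regions of whole ICUs, Kruskal-Wallis | 8.6% | 19.0% | 30.3% |
| Patient subgroup balanced within each ICU, t-test | 4.4% | 5.1% | 4.2% |
| Patient subgroup whose share varies between ICUs (assumed ICC of the share 0.1), t-test | 5.0% | 5.9% | 6.3% |

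The first row agrees with the formula. The number of regions is an assumption, because the article does not define them. Even at an outcome ICC of 0.20 the balanced subgroup stays at 3.3% and the unbalanced one reaches only 8.1%. The problem lies in the pooled prevalence and in between-centre comparisons.

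**The case against.** The strongest reply has four parts.

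- **Omission in a condensed article.** The analysis plan is not shown and may contain a centre effect. Nothing in the article states independence or excludes a centre term. This stands as a limit: the point must rest on the methods the article names, which in standard form assume independent patients, and not on what it leaves unsaid.
- **No interval and no geographical test are named.** A reader might infer that the study's confidence intervals are too narrow, or that its geographical comparison will produce false positives. The article does not support either. It plans no interval, and the geographical assessment could be purely descriptive. What can be said is conditional: a simple binomial interval, or a region test by the named methods, would understate uncertainty.
- **Most planned tests are patient-level.** A reader might infer that every planned test is invalid. The simulation contradicts this: subgroups spread within ICUs keep an error rate near or slightly below 5%, and uneven subgroup mix raises it only modestly.
- **Safeguards exist.** ICU selection, the sample-video check and blinded central reading all reduce differences between centres. They are not variance adjustments, however, and they do not remove differences in acquisition, clip selection or case mix.

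It would also overstate the article to say that it expects centre differences in general. Section 2.7.2 says only that image quality may vary.

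**Conclusion.** The point holds for the primary prevalence and for comparisons between centres or regions, in conditional form. How far precision would be overstated depends on an ICC that the article does not give. At 0.02 the effect is small; at 0.05 to 0.10 a nominal 5% region test has between two and a half and four times its intended error. The design effect concerns the standard error; on its own it does not bias the prevalence estimate.

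Because the study is described as primarily explorative and states no alpha or precision target, this is a cheap improvement that should be made. It does not invalidate the design.

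**What to change.** In section 2.7.3, or in the analysis plan if it does not already say so:

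- Report the primary prevalence with a 95% interval that is cluster-robust by ICU or comes from a logistic model with a random intercept for ICU.
- Analyse geography by regression with region as a factor and ICU as a random effect or GEE cluster. Adjust for collected case-mix variables (APACHE II/SOFA, reason for admission) and for device where both SDF and OPS were used.
- Include ICU in the outcome regressions. Simple tests of patient subgroups within ICUs can stay as described.
- Report the between-ICU variance or ICC, so that readers can see how much clustering there was.
- State the limit of the model: it corrects standard errors, but remaining differences in image quality between regions cannot be separated from true geographical differences.

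No new data are needed. Each centre enters its data in its own part of the database (section 2.6), so ICU is already recorded. The cost is some wording, a little more analysis work and somewhat wider intervals.

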### 2.4. SDF/OPS Imaging

Sublingual OPS and SDF imagings are used for microcirculatory imaging at the bedside with the potential of quantification both at the bedside and offline [33–35]. In short, the OPS and SDF analogue cameras are incorporated in handheld devices, emitting polarized, respectively, stroboscopic green light, with a wavelength within the absorption spectrum of haemoglobin, thereby depicting erythrocytes as black cells. The area of visualization is approximately 1 mm^2^. These techniques are described in detail elsewhere [2, 3]. Offline computer assisted analysis yields information on both convection and diffusion. Microvascular flow index (MFI) is calculated to describe convection in a semiquantitative way; the predominant flow in all quadrants of the SDF/OPS image is scored for different vessel sizes, using a scale ranging from 0 (no flow) to 3 (continuous flow). The averaged flow score yields the MFI for each image. MFI has been shown to correlate well with red blood cell velocity [36]. To obtain information on diffusion, several measures of functional capillary density are calculated, using a grid dividing the image into 16 segments. Every vessel crossing the grid is counted; furthermore, for each vessel crossing the grid, the type of flow using the MFI scale is used, a flow of 0 (no flow) or 1 (intermittent flow) is considered as nonperfused, whereas a flow of 2 (sluggish) or 3 (continuous) describes perfused vessels. By using these data, several measures of functional capillary density can be calculated, including proportion of perfused vessels (PPVs) and perfused vessel density (PVD). Dividing the numbers of perfused grid crossings by the total number of grid crossings yields the PPV; the PVD is calculated as the number of perfused grid crossings divided by the total grid length. In the same way, total vessel density (TVD) can be calculated. A detailed description of MFI and measures of functional capillary density can be found elsewhere [34, 35].

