#### 2.7.3. Statistical Analysis

Descriptive statistics will be used to describe the study population. Further statistical analysis will be conducted to relate the microcirculatory alterations to the severity of disease and other parameters. The primary outcome measure is the prevalence of microcirculatory alterations. There is no consensus about the thresholds for a “normal” and an “abnormal” microcirculation. Several researchers have reported on values of several microcirculatory variables in healthy volunteers; MFI of capillaries (<20 *μ*m) is reported to be 3.0 [2.9–3.0] (median [IQR]), 2.82 (0.1), and 2.97 (0.03) (mean(SD)) (IQR = interquartile range, SD = standard deviation) [5, 11, 42]. Therefore, one expects 95% of healthy subjects to have a small vessel MFI between 2.62 and 3 [11]. In healthy volunteers, PPVs (small vessels) well above 90% are described, whereas in septic patients, a capillary PPV of 78% (23%) is described [11, 42, 43]. In septic shock, norepinephrine dose >0.1 microgram/kg/min and a lactate >2 mmol/L were associated with a significantly lower PVD (12 [8–15] versus 14 [11–17] n/mm^2^ for norepinephrine dose >0.1 microgram/kg/min and 10 [8–13] versus 14 [11–17] n/mm^2^ for lactate >2 mmol/L), as well as a significantly lower PPV (80 [70–91] versus 100 [90–100]% for norepinephrine dose >0.1 microgram/kg/min and 82 [71–99] versus 93 [84–100]% for lactate >2 mmol/L) [44]. In uncomplicated major abdominal surgery, preoperative PPV (small vessels) was 89% (83–95) versus 79% (73–92) in patients who developed complications postoperatively [4]. In this study, ROC curves will be used to find cut off values of microcirculatory variables in relation to morbidity and mortality.

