## 3. Discussion

This study will be by far the largest cohort of in vivo microcirculation research. We aim to provide insight in the worldwide prevalence and distribution of microcirculatory alterations. The questions we hope to answer are the following:

Does the presence of microcirculatory alterations indicate impending bad outcome in terms of morbidity and mortality?Does the presence of microcirculatory alterations provide a more sensitive indicator of morbidity and mortality then conventional hemodynamic and oxygen derived parameters? Is the presence of microcirculatory alterations related to applied therapy, such as fluid therapy and vasopressors?Is there a difference between microcirculatory alterations in different patient (sub-) groups, and how are these geographically distributed, as well as over time?

We expect that the results of our study will make clinicians more aware of the presence and importance of microcirculatory alterations in daily practice, thereby leading to better identification of patients who are at risk of an unfavorable outcome. Furthermore, we hope to trigger researchers to develop methods enabling easier bedside evaluation of the microcirculation for detection of those at risk of “microcirculatory failure”, as well as interventions aimed at ameliorating the microcirculation. Hopefully, by putting the microcirculation in a central position in future ICU practice, outcome of critically ill patients will be improved.

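### Forward stepwise logistic regression is named as the test of association with mortality, severity scores and length of stay: selection makes its p-values invalid, and it is the only regression named although two of these outcomes are not binary

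*Protocol article*

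**What the plan says.** All of this is in the protocol article.

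- **Section 2.7.3, method.** With an opening limit to cases where it applies: "forward stepwise logistic regression analysis will be used to test for associations between the severity of microcirculatory dysfunction and illness severity, mortality, and length" (the last meaning duration of stay). No other regression is named.
- **Section 2.7.3, secondary outcomes.** "Secondary outcome parameters are the correlation between microcirculatory changes and macrohaemodynamic variables"; correlations of microcirculatory changes with "length of ICU/hospital stay, mortality, and SOFA/APACHE II scores" are listed as well. Subgroup differences are to be compared with a t-test or a nonparametric test.
- **Section 2.7.3, cut-offs.** "ROC curves will be used to find cut off values of microcirculatory variables in relation to morbidity and mortality". No cut-off is foreseen for length of stay or for the severity scores.
- **Section 2.4.** The density measures are described as "including proportion of perfused vessels (PPVs) and perfused vessel density (PVD"). With MFI and TVD, which the same section also describes, that makes four microcirculatory measures.
- **Section 2.5.** Demographics, admission reason, severity scores, haemodynamics, laboratory values and treatment are collected. All of these are possible candidates for a selection procedure.
- **Section 2.7.1.** The study is described as mainly explorative, and no alpha or power is given.

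The article does not say which side of each association is the dependent variable, what the entry level is, which variables are offered, or whether any variable is kept in regardless. Those details may sit in an analysis plan that is not shown, and their absence is not the point. The point is the method that the article does name.

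**The concern.** There are two separate problems.

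**Selection used as a test.** Forward selection admits a variable because it looks associated in the data. Its p-value is then computed as if the variable had been chosen beforehand. A variable that passes a 5% entry rule will nearly always show p < 0.05 in the final model, whether or not it has any effect. The four microcirculatory measures overlap, so one may also be left out only because a related one entered first. Which covariates sit beside a measure is decided by the data too, so adjustment for severity of illness is not assured. The cause is the selection, not the logistic model, so it applies to every outcome analysed this way.

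**Scale of the outcomes.** Ordinary logistic regression needs a binary dependent variable. Mortality is binary, but SOFA and APACHE II are numeric scores and length of stay is a duration. If these are the dependent variables, they would have to be split, and information is lost.

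What is at stake is the credibility of the secondary associations. Sections 3 and 4 expect the results to help identify patients at risk and to lead towards a goal-directed interventional study, so a spurious association could be carried into that trial's design.

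**Working it through.** **1. Sample size used.** Section 2.7.1 aims at ten times the size of earlier studies with 25 to 50 patients: 10 × 25 = 250 to 10 × 50 = 500. Section 4 gives approximately 500, the upper end. The calculations below use n = 500. The article has no power figure to reproduce.

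**2. Chance that a null variable enters (formula).** With k independent candidates, none related to the outcome, and an assumed entry level of 5%:

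P(at least one enters) = 1 − 0.95^k

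- k = 4 (the four microcirculatory measures): 1 − 0.8145 = 18.5%
- k = 10: 40%; k = 15: 54%; k = 20: 64%

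**3. The same by simulation.** Forward stepwise logistic regression was run with score-test entry at p < 0.05, n = 500 and 1,500 simulated studies per row. Four candidates are microcirculatory and have no effect of their own. The last column is one of these four, fixed in advance, in a model with all candidates and no selection. Number of candidates, event rate and correlation are assumptions.

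| Candidates | Event rate | Correlation | Other true predictors | Any candidate enters | At least one of the 4 measures enters | One pre-specified measure, p < 0.05 |
|---|---|---|---|---|---|---|
| 10 | 20% | 0 | none | 42.3% | 19.8% | 6.6% |
| 15 | 20% | 0 | none | 55.7% | 20.7% | 5.8% |
| 15 | 20% | 0.3 | none | 47.2% | 16.0% | 5.0% |
| 20 | 20% | 0 | none | 66.9% | 18.9% | 5.0% |
| 10 | 10% | 0 | none | 39.7% | 18.5% | 4.7% |
| 10 | 30% | 0 | none | 41.0% | 19.3% | 4.9% |
| 10 | 20% | 0.5 | none | 27.5% | 11.9% | 5.6% |
| 15 | 20% | 0.3 | three, log odds ratio 0.3 per SD | 100% | 20.5% | 5.3% |
| 15 | 20% | 0.5 | three, log odds ratio 0.3 per SD | 100% | 21.7% | 6.1% |

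The simulation error (one standard error) is about √(0.05 × 0.95/1500) = 0.6 percentage points near 5%, and √(0.2 × 0.8/1500) = 1.0 point near 20%.

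Three things follow.

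- At least one null microcirculatory measure enters in 11.9% to 21.7% of studies. Much of this is the four chances to enter (18.5% by the formula).
- With 15 candidates at correlation 0.3, adding true predictors related to the measures raises the figure from 16.0% to 20.5%.
- Once entered, a null measure had a Wald p-value below 0.05 in 98.0% to 99.7% of cases. The printed p-value repeats the entry rule and is not a test.

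**4. Cost of splitting a numeric outcome.** For a normal outcome and n = 500, the test on the full scale has approximate power Φ(atanh(r) × √(n − 3) − 1.96). At r = 0.125: 0.1257 × √497 = 2.80, and Φ(2.80 − 1.96) = Φ(0.84) = 80%. A median split keeps 2/π = 0.637 of the information, so 500 patients act like 0.637 × 500 = 318. The signal becomes 2.80 × √0.637 = 2.24, and Φ(2.24 − 1.96) = Φ(0.28) = 61%.

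Simulation (2,000 runs each) agrees:

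| r | Power, full scale | Power, median split |
|---|---|---|
| 0.10 | 60% | 42% |
| 0.125 | 80% | 60% |
| 0.15 | 92% | 76% |

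**The case against.** **The sentence is qualified.** It opens with a limit to cases where the method applies, and correlations are also planned for stay and the scores. A reader might infer that the plan will certainly run logistic regression on outcomes it cannot take. The article does not support that: the qualifier may restrict the method to outcomes that fit. But the same sentence lists all three and names no other regression, and the correlations as described carry no adjustment.

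**The direction is open.** The sentence speaks of associations and does not say what is dependent. If microcirculatory dysfunction, cut at a ROC threshold, were the dependent variable, scores and stay could be predictors in a logistic model. This stands, so the loss from splitting is conditional. It does not help with selection, which is the same problem in either direction.

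**The microcirculatory variable might be forced in.** That would remove most of the inflation. The article does not say so, and forward selection as named does not imply it.

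**The study is explorative.** This lowers the weight of the point and fits the secondary role of these analyses. It does not make a p-value from a selected model valid when the stated purpose is to test.

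**Two further inferences are not supported.** The Discussion asks: "Does the presence of microcirculatory alterations provide a more sensitive indicator of morbidity and mortality then conventional hemodynamic and oxygen derived parameters". A reader might take the stepwise model as the failed answer to that question. The article never assigns the question to this method, and the details of such a comparison may be left to an analysis plan. Nor does the article claim an association that holds after adjustment for severity; it lists severity as one of the variables to be related to dysfunction. Lack of assured adjustment limits how a result can be read, but it does not contradict a stated claim.

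**Conclusion.** The point holds for the method as named. Forward stepwise selection does not give valid p-values, confidence intervals or odds ratios for the selected variables, whichever of the three outcomes is analysed, and it does not assure adjustment for severity. The problem is not confined to mortality.

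Its size is about 12% to 22% of studies admitting at least one null microcirculatory measure, against about 5% to 7% for one pre-specified measure in a fixed model. This rests on a 5% entry level, 10 to 20 candidates of which four are microcirculatory, an event rate of 10% to 30% and correlations of 0 to 0.5. None of these is stated in the article except the four measures.

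The second part is conditional. If the scores or length of stay are the dependent variables, they must be split to be used, at a cost such as a fall from about 80% to 60% power at r = 0.125. That figure assumes a median split and a roughly normal outcome. It should not be carried over unchanged to length of stay, which need not be normal and can be ended by death.

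These are secondary analyses and the primary prevalence estimate is untouched. This should be fixed, but it is not a critical fault.

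**What to change.** Drop forward stepwise selection as a test and state the following instead.

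- **Mortality.** One pre-specified logistic model, with a named microcirculatory variable kept in as a continuous term and a short fixed list of collected covariates, for example APACHE II or SOFA, age and admission reason. Account for ICU, by a random intercept or cluster-robust standard errors.
- **Dependent variable.** State it for each association.
- **Severity scores.** Analyse on the full scale by linear or ordinal regression, leaving the severity scores out of the covariates.
- **Length of stay.** Use a model for durations, and say how deaths are handled.
- **Stepwise results.** If shown at all, label them exploratory and give no confirmatory p-values.

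Time in ICU before the measurement would be a natural further covariate. Section 2.5 does not list it, so it should not be assumed to be available.

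The cost is analysis wording. The covariates suggested above come from data groups that section 2.5 says are collected. The downside is that covariates must be named in advance and kept even when they are not significant.
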